### Study objectives and hypothesis

The primary objective of the DACAB-GI-2 study is to assess the effect of pantoprazole in the prevention of upper gastrointestinal mucosal injury in patients on DAPT after CABG. The secondary objective is to determine the cumulative incidence of upper gastrointestinal bleeding and major adverse cardiovascular events (MACE). We predicted that patients treated with pantoprazole for 12 months would have a significantly less upper gastrointestinal mucosal injury than patients treated with pantoprazole for 1 month.

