### Follow-up

Patients will be followed up to 12 months post-randomization unless dead. The outcome will be collected at 2±1 day, 9±2 days, 1 month (30±7 days), 3 months (90±7 days), 6 months (180±14 days), 9 months (270±14 days), and 12 months (360±14 days) after CABG surgery, respectively. Among them, the visits at 3 and 9 months after randomization are telephone calls. Each subject’s survival status (surviving/deceased), blood pressure, heart rate, body mass index, waist circumference, and adverse events (AEs) will be recorded on the CRF after each conversation. At 6 and 12 months post-randomization, routine laboratory tests and anesthesia EGD will be performed respectively. The endoscopist in the present study who evaluated the upper GI mucosal injury was blinded to random treatment allocations. In addition, computed tomographic angiography (CTA) or coronary angiography (CAG) is also required at 12 months post-randomization. Face-to-face adherence reminder sessions will take place at the initial pantoprazole dispensing and each study visit thereafter.

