### Outcome measurements

The primary outcome of this study will be the percentage of patients with gastroduodenal erosions and ulcers evaluated by EGD within 12 months after randomization. Gastroduodenal erosions and ulcers will be assessed according to the Lanza Endoscopic Scoring System [18] (0, normal; 1, mucosal hemorrhages only; 2, 1–2 erosions; 3, 3–10 erosions; 4, >10 erosions or an ulcer ≥3 mm). In addition, ≥1 ulcer with a diameter no less than 5mm will be grouped separately.

Secondary outcomes are as follows:Percentage of patients with gastroduodenal erosions and ulcers evaluated by EGD at 6 months after randomization.Cumulative rate of patients with upper gastrointestinal bleeding according to the modified TIMI criteria. According to the definition of non-CABG-related bleeding in the modified TIMI criteria, the severity of upper gastrointestinal bleeding is classified into 3 grades: major, minor, and minimal—(1) major: clinically overt signs of hemorrhage associated with a drop in hemoglobin of ≥5 g/dL; (2) minor: clinically overt signs of upper gastrointestinal bleeding, resulting in hemoglobin drop of 3 to <5 g/dL; and (3) minimal: any overt bleeding event that does not meet the criteria above.Percentage of patients with RE evaluated by EGD at 12 months after randomization. According to the Los Angeles classification, endoscopic reflux esophagitis was assigned a grade from A to D.Percentage of patients with RE evaluated by EGD at 6 months after randomization.

Other pre-specified outcomes (up to 12 months) include:The cumulative rate of patients with MACE (composite of cardiovascular death, myocardial infarctions, or stroke)The failure rate of grafts assessed by computed tomographic angiography or coronary angiography. Graft failure was assessed according to the modified Fitzgibbon classification [19]: stenosis ≥50% or occlusion of the graft or distal anastomosis (type B or O)The cumulative rate of patients with all-cause death

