### Definition of the end of study

The date on which the last subject completed the last follow-up was the endpoint of this studyDuring the follow-up period, if the patient’s biopsy pathological report showed that EGD detects precancerous lesions (e.g., atypical hyperplasia, low-grade or high-grade internal neoplasia, etc.) or malignant lesionsPatients randomized to the control group (1-month pantoprazole treatment group) should continue PPI treatment if GERD-Q questionnaire score ≥ 8, endoscopic findings of reflux esophagitis (LA-A and above), gastroduodenal mucosal injury of modified Lanza score of 4, or upper gastrointestinal bleeding at any time during the follow-up period

According to the ITT principle, all patients randomized in this study should be evaluated for primary and secondary endpoints regardless of changes in PPI treatment. Thus, patients in the 1-month pantoprazole treatment group required PPI treatment at any time after 1 month and could also be assessed for primary and secondary endpoints.

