## Discussion

Our previous study (DACAB-GI-1), a single-center prospective substudy of a RCT (DACAB, NCT02201771) [20], provided important reference data for the subsequent design of the DACAB-GI-2 trial. Briefly, patients aged 18–80 years with indications for elective CABG surgery were randomized to 1 year of open-label antiplatelet therapy comprising ticagrelor 90 mg twice daily plus aspirin 100 mg enteric-coated tablet, once daily; ticagrelor alone (90 mg twice daily); or aspirin alone (100 mg once daily). Prophylactic use of PPI was not a randomized intervention. It was recorded at 1, 3, 6, and 12 months post-CABG. Data of both upper gastrointestinal mucosal injury assessed by EGD and *H. pylori* infection detected by ^13^C urea breath test were obtained only at 1 year post-CABG, not at baseline [12]. In the present study (DACAB-GI-2), 232 subjects on DAPT after CABG will be randomized into two treatment groups (12- vs. 1-month treatment of pantoprazole); ^13^C urea breath test is done before enrollment and EGD is performed at 6 and 12 months after randomization, respectively.

A PPI selected in the present study was pantoprazole. Compared with the other PPIs, pantoprazole has a lower affinity for CYP2C19 and has the least interaction with other kinds of drugs, so it has higher safety and is less likely to cause AEs in patients when used in combination with dual antiplatelet agents [6, 7]. Whether the P2Y_12_ receptor inhibitor is clopidogrel or ticagrelor, pantoprazole is suitable in combination with it. In the present study, all patients will be treated with pantoprazole for at least 1 month after CABG to reduce the risk of perioperative gastrointestinal bleeding.

Patients undergoing CABG are those with more advanced coronary artery disease. EGD will not be performed preoperatively, perioperatively, and within 6 months of surgery, except in cases of emergency [21], because it is not considered to be in the patients’ best interest. In the present study, EGD will be performed at 6 and 12 months after randomization. The purpose of designing the first EGD at 6 months is not only to establish self-control but also to help identify patients with asymptomatic ulcers on time. Of particular importance, the early stages of esophageal and gastric neoplasms are asymptomatic as well. These patients are considered to have reached the endpoint of the study if they are diagnosed by EGD and biopsy at 6 months post-randomization.

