The present study includes two subgroup analyses, one is *H. pylori* infection status and the other is DAPT treatment. The results of our DACAB-GI-1 study [12] showed that the positive rate of *H. pylori* in patients receiving 1 year of antiplatelet therapy after CABG was 38.5%. After the study is completed, patients will be divided into the *H. pylori*-positive group and the *H. pylori*-negative group based on the results of the ^13^C urea breath test before enrollment; in addition, patients will be categorized into the clopidogrel plus aspirin group and the ticagrelor plus aspirin group according to their DAPT regimen after CABG. The difference of the primary and secondary endpoints will be compared in the above two subgroup analyses, respectively. Recently, the OPT-PEACE study [22] revealed the presence and severity of gastrointestinal mucosal lesions at 6 months or 12 months by magnetically controlled capsule endoscopy in patients receiving 12-month DAPT without PPI after PCI. To date, no study has reported visually evaluating the upper gastrointestinal mucosal injury (including RE) after 6 and 12 months of PPI treatment combined with two different DAPT by EGD yet.

In conclusion, the present study (DACAB-GI-2) probes the difference in preventing DAPT-related upper gastrointestinal mucosal injury after CABG between the different durations of pantoprazole treatment. The results should provide some confirmatory evidence for studies in relevant fields.

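### Only controls restart PPI when endoscopy shows reflux esophagitis, so the 12-month esophagitis outcome, read as a test of 12 versus 1 month, is biased toward no difference

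*Protocol article*

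**What the plan says.** The protocol article fixes five things that bear on this point.

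- **Restart rule.** Definition of the end of study lists the findings that put a 1-month patient back on PPI: a raised GERD-Q score, "endoscopic findings of reflux esophagitis (LA-A and above), gastroduodenal mucosal injury of modified Lanza score of 4", or upper gastrointestinal bleeding. The rule names the control group only. The wording speaks of continuing PPI, but for a control past month 1 this means restarting.
- **Outcomes.** Outcome measurements lists "Percentage of patients with RE evaluated by EGD at 12 months after randomization" and, separately, "Percentage of patients with RE evaluated by EGD at 6 months after randomization". RE is graded A to D on the Los Angeles scale, so the lowest grade that counts as RE is also the grade that triggers the restart.
- **Timing.** Follow-up states: "At 6 and 12 months post-randomization, routine laboratory tests and anesthesia EGD will be performed respectively". The Discussion adds: "EGD will not be performed preoperatively, perioperatively, and within 6 months of surgery, except in cases of emergency". The 6-month EGD is therefore the usual place where RE is first seen, about six months before the 12-month reading.
- **Analysis principle.** Definition of the end of study says that all randomized patients "should be evaluated for primary and secondary endpoints regardless of changes in PPI treatment".
- **Question asked.** Study objectives and hypothesis predicts that "patients treated with pantoprazole for 12 months would have a significantly less upper gastrointestinal mucosal injury than patients treated with pantoprazole for 1 month". The Discussion counts RE within such injury when it describes the gap in the literature: "visually evaluating the upper gastrointestinal mucosal injury (including RE) after 6 and 12 months of PPI treatment".

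**The concern.** The trigger for rescue is the outcome itself, at the same threshold, and the rescue is given in one arm before the outcome is read again. A control with RE at 6 months goes back on PPI. If the RE has healed by 12 months, that patient counts as free of RE at the later reading. No matching rule changes treatment in the 12-month arm.

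The event is still recorded in the 6-month outcome, but that outcome is silent on RE first appearing in months 6 to 12. No listed RE outcome covers the full year in a way that this restart cannot erase.

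What is at stake is interpretation. A null 12-month RE result could be read as showing that 1 month of PPI is enough for the esophagus, when the controls who had RE had been put back on the drug.

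**Working it through.** **The protocol's own figure.** The documents give no calculation for RE. The primary sample size (36% versus 18%, two-sided 0.05, 80% power, 186 evaluable) reproduces. The pooled formula gives 95 per arm (190), the unpooled formula 92 per arm (184), and exact binomial enumeration of the chi-square test at 93 per arm gives power 0.802. I use 93 per arm (186/2) and that exact method in the tables below.

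**Direction.** Let c6 be control RE at 6 months and h the share of it healed by month 12 because of the restart. The restart lowers control RE at 12 months by

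pull = c6 × h,

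and does nothing in the 12-month arm. Any positive h moves the control rate down.

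**Size, by assumption.** Neither c6 nor h is in the documents, so a range is shown in percentage points, with the number of 93 controls in brackets:

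| c6 | h = 25% | h = 50% | h = 75% |
|---|---|---|---|
| 10% | 2.5 (2.3) | 5 (4.7) | 7.5 (7.0) |
| 20% | 5 (4.7) | 10 (9.3) | 15 (14.0) |
| 30% | 7.5 (7.0) | 15 (13.9) | 22.5 (20.9) |

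**Worked example (all rates assumed).** RE at 6 months is 20% in controls and 10% in the 12-month arm. Of controls free of RE at 6 months, 5% develop it later. RE in the 12-month arm persists, and a share nt of those free of it at 6 months develop it later.

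- Control RE at either EGD = 0.20 + 0.80 × 0.05 = 24%.
- Control RE at 12 months = 0.20 × (1 − h) + 0.04, which is 19% at h = 25% and 14% at h = 50%.
- 12-month arm, both measures = 0.10 + 0.90 × nt.

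| nt | 12-month arm | Power, either EGD (control 24%) | Power, 12 months, h = 25% (control 19%) | Power, 12 months, h = 50% (control 14%) |
|---|---|---|---|---|
| 0 | 10% | 0.733 | 0.416 | 0.133 |
| 2.5% | 12.25% | 0.553 | 0.243 | 0.064 |
| 5% | 14.5% | 0.376 | 0.128 | 0.051 |

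The sign of the 12-month difference reverses once h exceeds 1 − (0.10 + 0.90 × nt − 0.04)/0.20, that is 70%, 59% and 47.5% for the three rows.

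**Cases that cut the other way.**

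- If half of the 6-month RE heals in both arms, nt = 0 gives 14% versus 5% at 12 months. The ratio is 2.8 against 2.4 at either EGD, so it is not diluted on that scale, although the difference falls from 14 to 9 points. With nt = 5% it is 14% versus 9.5%, a ratio of 1.5 against 1.7.
- The 6-month outcome alone (20% versus 10%) has power 0.484. That is above the 0.376 for either EGD at nt = 5%, so the either-EGD measure is not always the more powerful test.

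**Second parameterisation.** Take control RE without restart as 20% versus 8%, half of the control RE already visible at 6 months, and 80% of that healed. Observed control RE is 0.20 × (1 − 0.5 × 0.8) = 12%. The difference falls from 12 to 4 points, and power by normal approximation from 66% to 15%. The direction is the same.

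**The case against.** The strongest reply is that the authors foresaw this. Directly after the restart rule they say that restarted controls are still assessed for primary and secondary endpoints. That is a deliberate treatment-policy choice. It stands: the 12-month result is valid for the policy actually compared. A reader might infer that the outcome is invalid or that the intention-to-treat sentence is a mistake; the documents support neither. But the sentence does not remove the pull when the result is read as 12 versus 1 month, which is how the hypothesis is worded.

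A second reply is that the 6-month and 12-month outcomes together already hold everything seen at scheduled EGDs: RE healed by the restart was counted at 6 months, and later RE is counted at 12. At patient level this is right, but two separate percentages do not give the proportion of patients with RE at either examination. That proportion needs the patient-level data, which the two EGDs already supply.

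Third, an any-EGD outcome is not a clean 12 versus 1 month contrast either. Controls restarted for a Lanza score of 4 at month 6, or for GERD-Q or bleeding at or after it, can have new RE prevented in months 6 to 12. This stands, and it is why the added analysis should not become the RE comparison that decides the question, least of all when added late to an open-label trial.

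Fourth, RE is one secondary outcome for which the trial was not sized, the objectives do not name it, and the Discussion phrase that includes it describes a gap in the literature. All true, and it limits the weight of the point. A condensed article may also leave supplementary analyses to a fuller document. The point does not rest on their absence, though: the outcome definition and the control-only rule are both fixed here, and together they create the pull.

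**Conclusion.** The point holds as an issue of interpretation for one secondary outcome, worth fixing because the remedy is cheap. RE at 12 months validly compares 12 months of PPI with 1 month plus triggered restart. Read as 12 versus 1 month it is biased toward no difference.

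The direction rests on one assumption, that restarted PPI heals some RE. It applies to the effect of the restart itself; healing in the 12-month arm, where up to a month of double-dose PPI is tolerated, can offset it. The size cannot be derived from the documents, and every RE rate and power above is illustration.

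A reader might also infer that the primary outcome is diluted in the same way. The documents do not support that on the cumulative reading, which both the sample-size section and the primary outcome's 12-month window favour: a gastroduodenal lesion recorded at 6 months remains an event. The 6-month RE outcome is largely spared too, since before that EGD only symptoms, bleeding or an emergency endoscopy could trigger a restart.

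**What to change.** By dated amendment, before any analysis by arm:

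- Add RE of grade A or above at any EGD up to 12 months as a supplementary secondary analysis, labelled as added later.
- Keep the 6-month and 12-month RE outcomes as pre-specified, and describe the 12-month one as a treatment-policy result.
- Report how many controls had resumed PPI, by trigger.
- State that a null 12-month RE result alone will not be taken to show that 1 month of PPI is enough.

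The rescue rule and the primary outcome stay as they are.

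The cost is one extra analysis of data already collected. It comes late in an open-label trial (236 enrolled, 117 with 12-month follow-up complete), so it carries less weight than a pre-specified outcome, although the blinded endoscopist limits assessment bias. It reduces the dilution without removing it. Restarts before month 6, restarts for Lanza 4, GERD-Q or bleeding at or after month 6, and the H2 blockers allowed to controls only can still prevent or heal control RE. Nor will it always have more power than the 6-month outcome; its merit is that a restart triggered by RE cannot erase the event.

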### Statistical and analytical plans

The primary analysis was conducted according to the intention-to-treat (ITT) principle. All randomized subjects were included in the ITT analysis set. Subjects who received at least one dose of study medication and continued to receive the randomized intervention regimen (with or without study medication) 1 month after CABG were defined as the modified full analysis set (mFAS) population. Among them, subjects who completed the treatment according to the randomized protocol without major protocol violations and had a primary outcome assessment were included in the per-protocol set. Effectiveness analysis will be performed on the basis of mFAS. The safety analysis set consists of all the subjects who had taken at least one dose of study medication.

In this study, all subjects received pantoprazole treatment for at least 1 month after CABG. Due to the COVID-19 pandemic, some subjects are unable to return to the center for study drugs and/or follow-up 1 month after the randomization. Those subjects who are unable to receive subsequent randomization intervention will be excluded from the mFAS and not included in the effectiveness analysis. Considering the statistical power of the study, randomized subjects will be added until the effective randomized intervention number reaches the predetermined sample size.

All statistical analyses will be performed using SAS version 9.4 (SAS Institute Inc. SAS/STAT, Cary, NC, USA). Unless specified otherwise, the number of subjects (*n*), mean, standard deviation, median, maximum, and minimum will be provided for continuous variables, and the number of subjects and the percentage will be provided for categorical variables.

The baseline in this study will be defined as the last available (non-missing) assessment (scheduled or unscheduled) before or on the same day as the first dose of study treatment.

The chi-square test will be applied as the main analysis of the primary efficacy endpoint, and multiple sensitivity analyses will be performed to support the main analysis. For secondary and exploratory efficacy endpoints, analysis of covariance, Wilcoxon-Mann-Whitney test, log-rank test, a mixed-effects model for repeated measures, and negative binomial regression model will be applied based on the type of data in the analysis. Descriptive statistics will be provided to summarize safety endpoints.

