### Trial status

Recruitment starts on October 20, 2019. A total of 236 patients were enrolled in the DACAB-GI-2 trial between October 2019 and February 2022. Among them, 183 patients who received an effective randomized intervention were included in the study. A 12-month clinical follow-up has been completed in 117 patients. Due to the outbreak of Omicron in March 2022, Shanghai is currently still in a city-wide lockdown. Some follow-up visits have had to be postponed for 2 to 3 months. The duration of the trial was extended with the approval of the ethics committee, and it is planned to be completed in June 2023. The version of this protocol is 4.0 (date 20220225).

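### The plan names two incompatible populations for the primary efficacy comparison: all randomized patients (ITT), and an mFAS that drops patients at month 1 and replaces them

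*Protocol article*

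**What the plan says.** Two places commit the trial to intention-to-treat. Statistical and analytical plans opens with "The primary analysis was conducted according to the intention-to-treat (ITT) principle" and adds "All randomized subjects were included in the ITT analysis set". Definition of the end of study repeats the principle: "all patients randomized in this study should be evaluated for primary and secondary endpoints regardless of changes in PPI treatment".

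The same statistical section then says "Effectiveness analysis will be performed on the basis of mFAS". To be in the mFAS a patient must have taken at least one dose and have "continued to receive the randomized intervention regimen (with or without study medication) 1 month after CABG". Patients whom the pandemic kept from returning for study drug and/or follow-up, and who could not receive the later intervention, "will be excluded from the mFAS and not included in the effectiveness analysis". To protect power, "randomized subjects will be added until the effective randomized intervention number reaches the predetermined sample size".

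Trial status reports 236 patients enrolled by February 2022, of whom "183 patients who received an effective randomized intervention were included in the study". Sample size gives two candidate targets: 186 required for 80% power, and 232 after allowing for 20% drop-out.

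**The concern.** The primary outcome, endoscopic erosions and ulcers, is described in the same section as the primary efficacy endpoint. Both population statements therefore apply to it, and the headline result could depend on which is followed.

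This is also not a routine full-analysis-set exclusion. Both arms take pantoprazole for the first month, so the one-dose condition should remove few patients. The condition that matters is continuing the assigned regimen at month 1, which is when the two strategies separate. It is met or failed after allocation is known to patient and investigator. It can act unequally, because only the 12-month arm needs more drug from the center, while a control patient follows the assigned regimen by stopping.

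If the patients lost differ between arms in number and in underlying risk, the retained groups are no longer the randomized groups. Replacing them restores the count, not the comparability.

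**Working it through.** **1. The statements side by side.** ITT set: everyone randomized, whatever happens to PPI treatment. Effectiveness set: a subset defined by an event at month 1, with the remainder expressly left out. No reading makes both the basis of the primary efficacy test.

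**2. The plan's own sample size.** Inputs from Sample size: 36% versus 18%, two-sided α 0.05, 80% power, 1:1. The pooled normal-approximation formula gives 95 per arm (190 in total); the unpooled form gives 92 per arm (184). The stated 186 lies between them. Drop-out: 186/(1 − 0.20) = 232.5, against 232 stated. These figures are not in dispute.

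**3. Patients outside the effective group.** 236 − 183 = 53; 53/236 = 22.5%.

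**4. What the top-up rule implies.** At retention 183/236:
- target 186: 186 × 236/183 = 239.9, about 240 randomized;
- target 232: 232 × 236/183 = 299.2, about 299 randomized.

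Both assume that the retention seen so far continues.

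**5. One dilution scenario.** Assumptions: 118 per arm (236/2); mFAS rates of 36% and 18%; k excluded patients in the 12-month arm, each with control risk; excluded control patients also at 36%; all 236 with an outcome. The as-assigned 12-month rate is [(118 − k) × 0.18 + k × 0.36]/118.

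| k | 12-month rate | Difference from 36% | Power, 118 per arm |
|---|---|---|---|
| 0 | 18.0% | 18.0 points | 88% |
| 20 | 21.1% | 14.9 points | 72% |
| 35 | 23.3% | 12.7 points | 57% |
| 45 | 24.9% | 11.1 points | 46% |

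This is the gap between an on-regimen effect and an as-assigned effect. It does not measure selection bias.

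**6. Selection bias with no true effect.** Assumptions: 36% risk in each full arm, 118 per arm, 53 excluded in total, and risk r among the excluded. The retained rate in an arm that loses x patients is (118 × 0.36 − x × r)/(118 − x).

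| Excluded, 12-month / 1-month | r | Retained rates | Spurious difference | Type I error |
|---|---|---|---|---|
| 40 / 13 | 36% | 36.0% / 36.0% | 0 | 5% |
| 27 / 26 | 51% | 31.5% / 31.8% | −0.2 points | 5% |
| 35 / 18 | 51% | 29.7% / 33.3% | −3.6 points | 8% |
| 40 / 13 | 51% | 28.3% / 34.1% | −5.8 points | 13% |

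Bias needs both unequal loss and a different risk in those lost. The sign reverses if the imbalance runs the other way: 13 / 40 at 51% gives +5.8 points.

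**The case against.** The strongest defence is that these exclusions come from a pandemic and so have nothing to do with the outcome. If they are also balanced by arm, or unrelated to risk, step 6 shows essentially no bias. That stands as a possibility. But an external cause does not guarantee equal effect when only one arm needs further drug.

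A reader might infer that patients leave mainly the 12-month arm. The documents do not support this as fact. The trigger is failure to return for drug and/or follow-up, so control patients can be excluded too, and no counts by arm are given.

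A reader might also take the mFAS to contain only patients who stayed on pantoprazole. Its wording points to a check at 1 month, with or without study medication; completing treatment is the per-protocol condition. Someone who stops later appears to remain in the mFAS.

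Nor are all 53 shown to be permanent exclusions. No reasons are given, and some recent enrollees may not have reached month 1. Enrolling 236 against 232 is not an anomaly, because the top-up rule provides for it.

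Finally, the article promises several sensitivity analyses, and an unseen analysis plan may detail them. None is identified as ITT here, and a sensitivity analysis would not settle which population is primary.

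**Conclusion.** The contradiction is explicit and must be resolved before analysis. The plan promises ITT twice, yet bases effectiveness on a set with post-randomization exclusions. That set puts the randomized comparison at risk when the arms begin to diverge, and replacement does not repair it.

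The firm number is 53 of 236 (22.5%) not counted as effectively treated at the status date, with no reasons given. How much bias this causes, and in which direction, cannot be derived. The 14.9 to 11.1 points rest on assumed mFAS rates of 36% and 18%, and on 20 to 45 excluded 12-month patients carrying control risk. A claim that the mFAS will overstate the effect by about 3 to 7 points would turn that single scenario into a finding. Under equal risk in the excluded the bias is nil.

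The top-up target is a real ambiguity: 186 and 232 imply about 240 or 299 randomized.

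**What to change.** - State that the primary efficacy analysis includes all randomized patients in their assigned arm, using every endoscopy obtained whether or not the later drug was received.
- Handle missing endoscopies with a method that reflects loss of assigned treatment, for example imputing excluded 12-month patients without drug under control-like risk, and add a tipping-point check. Imputing by arm without regard to treatment received would draw on patients still taking the drug and largely return the mFAS estimate.
- Keep the mFAS as a supportive analysis, with exclusions tabulated by arm and reason.
- Replace the predetermined sample size in the top-up rule with one stated number, and say whether it counts randomized or retained patients.

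The cost is a wording amendment and some imputation work. The estimate and power may look less favourable than on the mFAS.

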### Randomization and allocation

The eligible subjects will be randomized in a ratio of 1:1 to the 12-month or the 1-month pantoprazole treatment group. Block randomization with a block length of four will be applied. The randomization numbers will be generated in a list using SAS 9.4 (SAS Institute Inc., Cary, NC, USA) and sealed in the envelopes (Fig. 1).

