### Sample size

According to the results of the preliminary study, the cumulative incidence of severe gastric and duodenal bulb erosion and ulcers of the 1-month PPI treatment group is assumed to be 36%, and that of the 12-month PPI treatment group was assumed to be 18%. Based on a two-sided *α* of 0.05 and a randomization ratio of 1:1, a total of 186 subjects are required to provide a power of 80%. Considering a 20% drop-out rate, the sample size of 232 subjects was determined.

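### The unadjusted chi-square is valid but leaves baseline H. pylori status unused; an adjusted main analysis and an interaction-based subgroup rule would be cheap improvements

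*Protocol article*

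**What the plan says.** Under Statistical and analytical plans, the article fixes the main test: "The chi-square test will be applied as the main analysis of the primary efficacy endpoint". The same sentence adds supporting sensitivity analyses that it does not describe. It names no adjustment factor.

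Under Randomization and allocation, the method is "Block randomization with a block length of four will be applied", again with no stratification factor.

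Under Scope of study data, a urea breath test for H. pylori is required before enrolment. The Discussion then picks out two factors for subgroup analysis, H. pylori status from that test and the DAPT regimen after CABG, and says: "The difference of the primary and secondary endpoints will be compared in the above two subgroup analyses, respectively". It mentions neither a treatment-by-factor interaction nor exploratory status.

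**The concern.** The plan treats H. pylori status and DAPT regimen as the two factors worth separate study. H. pylori is known before randomisation, yet the main comparison as stated ignores both. Two things are at stake.

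- **Precision and chance imbalance.** If H. pylori predicts lesions, an unadjusted comparison gives up some power, and a chance difference in H. pylori prevalence between arms shifts the estimated treatment difference.
- **Subgroup claims.** If the Discussion sentence means a test of 12 versus 1 month inside each level, each test is small. One level reaching significance and the other not would be common even when the effect is the same in both, and could be reported as benefit confined to one kind of patient.

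**Working it through.** **Inputs from the article.** Sample size section: 36% (1 month) versus 18% (12 months), two-sided alpha 0.05, 80% power, 186 evaluable, 1:1 (93 per arm). Discussion: 38.5% H. pylori positive, measured one year after CABG in the earlier study and used here as a stand-in for baseline prevalence.

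**Assumed, because the article gives no figure.** Odds ratio of H. pylori with lesions: 1 to 5. Split of DAPT regimens: 50/50 to 20/80.

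**1. The plan's own figure.**
- Unpooled variance: n per arm = (1.960 + 0.842)² × (0.36×0.64 + 0.18×0.82) / 0.18² = 91.6, so 92 per arm and 184 in total.
- Pooled variance: 94.3, so 95 per arm and 190 in total.
- The stated 186 lies between these. Normal-approximation power at 93 per arm is 79.4%. The sample size fits a plain two-proportion test.

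**2. Chance imbalance in H. pylori.**
- SD of the between-arm difference in prevalence = √(2 × 0.385 × 0.615 / 93) = 0.071, or 7.1 points.
- 1.96 × 7.1 = 14 points, so a gap larger than 14 points has about a 5% chance.
- With an overall risk of 36%, an odds ratio of 2 gives risks of about 30% (negative) and 46% (positive); an odds ratio of 5 gives about 22% and 58%. The shift in the treatment difference from a 14-point gap is 0.14 × 16 ≈ 2 points to 0.14 × 36 ≈ 5 points.

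**3. Power with and without adjustment.** Simulation of 200,000 trials per row, 93 per arm, marginal rates 36% versus 18%, one binary factor with 38.5% prevalence, Cochran-Mantel-Haenszel (CMH) without continuity correction:

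| Factor odds ratio | Chi-square | CMH |
|---|---|---|
| 1 | 80.1% | 79.5% |
| 1.5 | 80.2% | 79.9% |
| 2 | 80.3% | 80.5% |
| 3 | 80.1% | 81.7% |
| 5 | 80.3% | 84.3% |

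A 50/50 factor gives the same pattern (odds ratio 3: 80.2% versus 81.8%; odds ratio 5: 80.2% versus 83.8%). With no treatment effect, rejection rates are 5.2–5.4% unadjusted and 5.0–5.2% adjusted.

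**4. Separate subgroup tests under one uniform effect.** With 36% versus 18% in every patient and 186 evaluable, power within a subgroup of n per arm is Φ[(0.18√n − 1.96√(2×0.27×0.73)) / √(0.36×0.64 + 0.18×0.82)].
- H. pylori positive, about 72 patients: 40%. Negative, about 114 patients: 58%.
- Exactly one significant: 0.401 × (1 − 0.584) + 0.584 × (1 − 0.401) = 0.517, about 52%. Both significant: 0.401 × 0.584 = 0.234; the simulation gives 24%.
- DAPT regimen at 50/50: 50% and 50%, exactly one 50%. At 20/80: 23% and 70%, exactly one 61%.
- With no effect at all, exactly one of the two levels of a factor is significant about 10% of the time.

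**5. Interaction test.** Suppose the full effect sits in the H. pylori-positive subgroup only, about 35.8 positive and 57.2 negative patients per arm. SE = √[(0.2304 + 0.1476)/35.8 + (0.2304 + 0.2304)/57.2] = 0.136. Power = Φ(0.18/0.136 − 1.96) ≈ 26%; for a 50/50 factor it is 27%.

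**The case against.** The strongest reply is that nothing here is wrong. Randomisation is not stratified, so no design factor has to be carried into the analysis. The chi-square holds its type I error, chance imbalance is already covered by that error rate, and the test matches the sample-size calculation. All of that stands. A reader might infer that the primary analysis is defective or wastes substantial information; the document does not support this. The gain depends on a prognostic strength it does not give, and it is nil or slightly negative up to an odds ratio of 2. Permitted H. pylori eradication during follow-up could weaken the link between baseline status and later lesions.

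A reader might also infer that the two factors enter only through subgroups. The article promises several sensitivity analyses without describing them, and an adjusted model could be among them.

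On subgroups, the sentence is one line in a journal Discussion. It does not say that separate p-values will be used or that interaction will go untested, and a SAP that is not shown may settle both. Separate comparisons are the natural reading, not a certain one, so the 52% is conditional on it.

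Finally, 117 patients had completed 12 months when the article was written, in an open-label trial. Changing the main test then needs a dated amendment made without sight of outcomes by arm, which is somewhat more than a change of wording. This limits how the change is made; it does not remove the case for it.

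**Conclusion.** This is a worthwhile improvement, not the correction of an error. The main analysis as stated is valid but leaves out a baseline factor that the plan singles out and already collects. The expected benefit is modest: about nil up to an odds ratio of 2, with a loss of roughly 0.6–0.7 power points if the factor is not prognostic, 1–2 points at 3 and about 4 points at 5. In addition, the estimate no longer moves with a chance H. pylori imbalance. These figures assume 186 evaluable patients, 38.5% prevalence at baseline and adjustment for one binary factor.

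The subgroup part is conditional. If separate tests are meant, a significant-in-one-level-only pattern for H. pylori would arise in about half of trials with a uniform effect. An interaction test avoids that inference but has little power (26–27% even in the extreme case), so either way the subgroup results can only be exploratory.

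The absence of stratified randomisation is not part of the point to be fixed: 236 patients had already been enrolled against a target of 232.

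**What to change.** Before database lock, in a dated amendment or the SAP, written without sight of outcomes by arm:

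1. Make the main analysis a CMH test with a stratified risk difference, or logistic regression with a standardised risk difference, adjusted for H. pylori status from the pre-enrolment breath test and for DAPT regimen. Keep the unadjusted chi-square as a named sensitivity analysis.
2. Define DAPT regimen as the one planned or started at randomisation. The Discussion says only that it is the regimen after CABG, which could pick up later switches.
3. State that any subgroup claim rests on the treatment-by-factor interaction estimate with its confidence interval, that the treatment effect and confidence interval are shown for each level, and that these analyses are exploratory.

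The cost is wording and programming. The breath test is already required before enrolment, and regimen is already needed for the planned subgroups. No further patients or visits are needed, and the randomisation stays as it is.
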